## Abstract

**Background:**

Vision is an important and defining element of laparoscopy and significantly affects the outcome of surgery in terms of time, error, and precision. Several new imaging systems have become available for laparoscopic surgery, including three-dimensional (3D) high-definition (HD) and two-dimensional (2D) ultra-high-resolution (4K) monitors. 3D HD systems offer a number of potential benefits to surgeons and patients over traditional 2D systems, including reduced operating time, blood loss, and hospital stay. However, the performance of 3D systems against the new, ultra-high definition 4K systems is barely known and highly controversial. There is a paucity of studies comparing them in clinical settings. The aim of this study is to compare 2D 4K and 3D HD perspectives in gastric bypass surgery.

**Methods:**

Forty-eight patients with an indication for gastric bypass will be randomized to receive laparoscopic gastric bypass surgery using either 2D 4K or 3D HD systems. The operations will be performed by a well-coordinated team of three senior surgeons. The primary outcome is operative time. Secondary outcomes include intraoperative complications, blood loss, operator workload as assessed by the validated Surg-TLX questionnaire, and postoperative complications according to the Clavien-Dindo classification. An interim analysis is planned after enrollment of 12 participants for each group.

**Discussion:**

This prospective, randomized trial is designed to test the hypothesis that the use of a 3D HD system will result in a significant improvement in operative time compared to a 2D 4K system in bariatric surgery. The objective is to provide clinical evidence for new laparoscopic imaging systems and to evaluate potential benefits.

**Trial registration:**

This trial is registered at clinicaltrials.gov under the identifier NCT05895058. Registered 30 May 2023. BASEC2023-D0014 [Registry ID Swissethics, approved 3 May 2023]. SNCTP000005489 [SNCTP study register, last updated 13 July 2023].

**Supplementary Information:**

The online version contains supplementary material available at 10.1186/s13063-024-07983-4.

## Administrative information

Note: the numbers in curly brackets in this protocol refer to SPIRIT checklist item numbers. The order of the items has been modified to group similar items (see http://www.equator-network.org/reporting-guidelines/spirit-2013-statement-defining-standard-protocol-items-for-clinical-trials/).

Role of sponsor {5c}	[name] is the Sponsor-Investigator and one of the operating surgeons in the study. Together with his surgical team, he will recruit patients, inform them about the study and obtain informed consent. He will be responsible for performing the surgeries and collecting the data. After surgery, he will provide the data to the other authors of the study for further processing, analysis, and interpretation, and will write the report. He has final authority over all activities.

## Introduction

### Background and rationale {6a}

Laparoscopy has become an essential part of modern surgery. However, there are still some limitations to this technique [1]. In particular, vision is an important and defining element of laparoscopy and significantly affects the outcome of surgery in terms of time, intraoperative errors, and surgical precision [2]. Since the introduction of laparoscopic surgery, this surgical practice has evolved rapidly and many technological advances have been made to overcome the shortcomings of early endovision systems [3]. These advances have focused on improving the quality of vision and compensating for the loss of binocular depth perception [4]. Particularly for novices, the reduction from real three-dimensional (3D) vision to virtual two-dimensional (2D) vision is challenging and associated with a slower learning curve. Recently, several new imaging technologies have become available for laparoscopic surgery, including stereoscopic 3D high-definition (HD) and 2D ultra-high-resolution (4K) monitors. These developments in high-definition and stereoscopic imaging have attempted to overcome the major technical limitations of laparoscopy [5–7].

In experimental and clinical settings, several studies have been published in recent years suggesting that 3D systems offer a number of potential benefits to surgeons and patients compared to conventional 2D systems [2, 5]. Compared to the 2D system, 3D systems increase the subjective impression of safety and efficiency and consequently provide better surgeon confidence during surgery due to the depth perception that enables better visualization [2, 8]. In addition, the 3D HD imaging system significantly reduces operating time and blood loss, as well as shortens hospital stays [2]. This is critical as prolonged operative time and immobilization are known to be independent predictors of post-operative complications [9]. In 2018, the European Association for Endoscopic Surgery (EAES) published recommendations that 3D systems should be used in clinical practice to reduce operative time [2]. Despite these recommendations and the advantages of 3D imaging, the system is not widely used due to the need to train surgical staff in the technology and modernize operating rooms, both of which are associated with higher costs [10]. In addition, the potential superiority of 3D systems over new ultra-high-definition (4K) systems remains unproven and therefore highly controversial.

Indeed, with the introduction of 4K monitors, 2D rendering can provide four times the visual quality of conventional HD. This system improves vision through ultra-high resolution, a wider range of colors, and enhanced visualization, potentially providing a more realistic image and stronger monocular depth perception. The improved visualization allows surgeons to see tissue structures up close and evaluate them more accurately. Both novice and experienced surgeons have been shown to have better outcomes in terms of operating time and errors when using the 2D 4K system compared to the 2D HD system [11]. Currently, the use of the new 2D 4K technology is expanding and may become the standard in the near future [12]. However, the major limitation of 2D laparoscopy is still the lack of depth perception. The surgeon must compensate by using secondary visual reference points to correctly interpret the 2D laparoscopic image. This disadvantage can potentially increase the surgeon’s workload, risk of error, and operating time.

The choice of laparoscopic tools should be based on the best available evidence, but there is a paucity of studies comparing 3D HD and 2D 4K systems in the clinical setting. Particularly for more complex procedures, there are few, although some studies have shown that the more complex the laparoscopic procedure involving multiplane interactions, the more surgeons benefit from 3D visualization [12–15]. Additionally, Dunstan et al. [13] compared 3D with 4K laparoscopy in performing cholecystectomies, while Kanaji et al. [14] performed a comparison in performing laparoscopic gastrectomy for gastric cancer. The conclusion of both studies was that the 3D HD laparoscopic system did not reduce operative time and provided similar clinical outcomes compared to 2D 4K.

In summary, the benefits of imaging systems can only be truly addressed in clinical trials with appropriately powered sample sizes. This prospective randomized controlled trial comparing 3D HD and 2D 4K perspectives in gastric bypass surgery was designed for this purpose.

### Objectives {7}

We aim to investigate the hypothesis that the use of the 3D HD system will result in a significant improvement in operative time compared to a 2D 4K system in bariatric surgery. This hypothesis is based on our recently published randomized controlled preclinical study comparing 2D 4K and 3D HD using tasks performed on a pelvitrainer model by experts and medical students. Participants in both groups, experts and medical students, achieved significantly better results, including faster task completion times and fewer errors, with the 3D HD imaging system compared to the 2D 4K system [8]. Based on these preclinical results, we will now conduct the randomized trial in a clinical setting. Due to the standardized surgical procedure and the comparable conditions of gastric bypass surgery, we expect to explore significant differences. In addition, to provide a comprehensive overview of the comparison of 2D 4K and 3D HD laparoscopy in a clinical setting, we will evaluate surgeon workload and intraoperative and postoperative complications, including hospital length of stay.

### Trial design {8}

This study is designed as a single-center, parallel-group, superiority, randomized, controlled, prospective trial. All patients will have gastric bypass surgery and will be operated with 3D HD or 2D 4K imaging depending on the intervention group assignment. The patient allocation is 1:1.

## Methods: participants, interventions, and outcomes

### Study setting {9}

This study is a single-center study and will be conducted at Clarunis, University Center for Gastrointestinal and Liver Diseases (St. Clara Hospital and University Hospital Basel), which is a certified reference center for bariatric and metabolic surgery with a caseload of nearly 80 complex bariatric surgeries per year. The surgeries are performed by three experienced senior bariatric surgeons from Clarunis at the University Hospital Basel.

### Eligibility criteria {10}

#### Inclusion criteria

Patients must meet the following criteria to be eligible for the study:Patients with an indication for gastric bypass according to the Swiss Morbid Obesity Group (SMOB) guidelines: age ≥ 18 years, BMI ≥ 35, and a cumulative 2 years of controlled conservative diet without weight lossSigned informed consent

#### Exclusion criteria

Patients who meet any of the following criteria at the screening visit are not eligible for the study:Patients who are ineligible for gastric bypass based on one or more of the following criteria: BMI ≥ 50, lack of adequate weight loss therapy for 2 years, malignant disease, Child A cirrhosis, Crohn’s disease, carcinoma patients, severe mental illness requiring treatment (not due to obesity that has led to more than one inpatient psychiatric hospitalization in the last 2 years), chronic substance abuse, lack of compliance (missed appointments, inability to cooperate), lack of understanding of the requirements and conditions of postoperative therapy and treatment (confirmed by the specialist)Non-signed informed consent

### Who will take informed consent? {26a}

Patients evaluated for gastric bypass according to the SMOB guidelines at the Clarunis multidisciplinary obesity conferences are recruited into the clinical trial by the operating surgeon. The surgeon will inform the patient of the clinical trial and obtain informed consent. If the patient agrees to participate in the study and signs the informed consent, he or she will be enrolled in the study.

### Additional consent provisions for collection and use of participant data and biological specimens {26b}

This is not applicable; there is no collection and use of participant data or biological specimens in ancillary studies.

## Interventions

### Explanation for the choice of comparator {6b}

The comparison group to 2D 4K imaging for performing laparoscopic gastric bypass is 3D HD imaging. The EAES has recently made recommendations that 3D systems should be used in the clinical setting to reduce operative times [2]. However, its use is still limited due to higher costs and lack of familiarity. Other weaknesses of 3D imaging to date have been the need to wear special glasses and the reported side effects for surgeons associated with 3D vision systems such as dizziness, eye fatigue, nausea, and headaches [11]. However, rapid advances in 3D imaging technology over the past two decades appear to have successfully overcome previous barriers to widespread clinical use. Current 3D systems capture separate images using either two separate rod lenses or two separate chips on a scope tip to provide two vertically separated images that simulate binocular vision [16]. These improvements have made 3D imaging more user-friendly, with fewer side effects, and its benefits are becoming more apparent.

### Intervention description {11a}

The two medical devices to be compared have components that are as similar as possible and are used under the same conditions. The brand of both laparoscopic towers and all listed components are from Karl Storz SE & Co., Tuttlingen, Germany. The two camera systems used are a 2D 4K system module (TC304 IMAGE1 STM 4 U-LINK) equipped with a 30° field of view and a 10-mm diameter laparoscope (HOPKINS Optic) and a 3D HD system module (TC300 IMAGE1 STM D3-LINK and TC302 IMAGE1 STM H3-LINK) equipped with a 30° field of view and a 10.3-mm diameter laparoscope (TIPCAM1 SPIES 3D LAP Optic). The 4K endoscopy tower is equipped with a 32″ 4K monitor (TM 343) with a screen resolution of 3840 × 2160, while the 3D endoscopy tower is connected to a 32″ 3D monitor (TM 323) with a corresponding screen resolution of 1920 × 1080. 3D glasses, also from Karl Storz SE & Co., Tuttlingen, Germany, are used for the 3D system. The surgeons are positioned exactly one and a half meters in front of the monitor to ensure the effect of both the 4K and 3D imaging systems.

The comparison of the two laparoscopic imaging systems 2D 4K and 3D HD is performed during a gastric bypass surgery. This procedure provides a high level of comparability as it is highly standardized, complex, and involves many multiplane interactions. These gastric bypass operations are all performed by three defined senior surgeons of the Clarunis bariatric surgery team as described in detail above.

### Surgery procedure

All patients will receive a laparoscopic Roux-en-Y gastric bypass (LRYGB), an effective surgical treatment for obesity (Fig. 1). Briefly, the upper part of the stomach is separated from the rest of the stomach below the esophagus by stapling sutures, creating a gastric pouch. The upper part of the small intestine is cut and one limb is attached to the stomach pouch. The small intestine, which comes from the blindly closed stomach and contains the digestive juices from the duodenum, is sewn into this raised loop of small intestine. This bypasses the rest of the stomach (= bypass) [17].

**Fig. 1 Fig1:**
[figure not shown]
Visualization of the gastric bypass operation

### Criteria for discontinuing or modifying allocated interventions {11b}

Gastric bypass surgery and its pre- and post-operative procedures are performed as standard. The study only influences the choice of laparoscopic imaging used during surgery. Consequently, the criteria for stopping or modifying the allocated procedures for a given subject will depend on the responsible operator in consultation with their multidisciplinary obesity team and within the given national guidelines of the SMOB. If the indication is no longer given due to changed inclusion or exclusion criteria, the intervention will not be performed. In addition, patients may withdraw from the study at any time for any reason without consequence.

Patients excluded prior to gastric bypass surgery will be replaced to maintain the required number of procedures for comparison. Patients who are excluded after surgery because they do not return for their first post-operative visit at 3 months, and therefore no post-operative follow-up can be documented, will not be replaced, as this follow-up is only one of the secondary endpoints of the study.

### Strategies to improve adherence to interventions {11c}

This is not applicable, as the operations are performed according to the standard for gastric bypass surgery and are therefore already subject to its strict regulations. This study only defines the laparoscopic imaging used. Proper planning and execution is the responsibility of the operating surgeon. Monitoring is defined in a separate monitoring plan according to the ISO 14155 guidelines.

### Relevant concomitant care permitted or prohibited during the trial {11d}

This is not applicable; no relevant concomitant care and interventions are allowed or prohibited during the study. If unexpected events occur during surgery that require additional interventions, this will be documented in detail and mentioned and considered in the analysis.

### Provisions for post-trial care {30}

This is not applicable as both medical devices (3D HD and 2D 4K) are already routinely used in bariatric surgery. Therefore, there are no additional risks associated with the conduct of the study, and no consequences are expected for patients. In case of problems or complications, the patient will be followed up as part of the post-operative procedure of a general gastric bypass surgery.

### Outcomes {12}

#### Primary

The primary outcome of our prospective study is operating time. It is the most important and decisive parameter in our comparison between 3D HD and 2D 4K and potentially influences our secondary outcomes. In summary, operative time has a significant impact on a patient’s postoperative outcome and is therefore of considerable clinical relevance. Operative time is measured and documented during the performance of laparoscopic gastric bypass. It is defined as the time from the beginning of the operation by the incision of the skin to the end of the operation by the end of the skin suture. The operative time is the difference between these two times and is documented in minutes.

#### Secondary

Secondary outcomes include intraoperative complications, operator workload, and postoperative complications. Intraoperative complications are assessed descriptively by the surgeon’s documentation in the operative report. These include major bleeding, injuries or burns to surrounding organs (e.g., stomach, esophagus, spleen, liver), circulatory problems, or unexpected intra-abdominal findings that deviate from the standardized surgical procedure or expected extent and must be noted in the operative report. Blood loss is recorded and documented quantitatively in milliliters. In addition, a postoperative Hb control is performed if indicated by intraoperative complications and the Hb decrease is determined. Immediately after each surgery, the surgeon completes the Surg-TLX questionnaire, a validated multidimensional measure of surgical workload. The Surg-TLX defines workload based on six dimensions: mental demands, physical demands, temporal demands, task complexity, situational stress, and distractions. The condition of the operating surgeon has a great influence on the outcome of an operation. Especially when using 3D imaging, some undesirable side effects have been reported. It is important to determine the subjective workload of the surgeon when using modern imaging and performing a more complex procedure. Postoperative complications are influenced by many factors, including operative time and intraoperative complications. It is important to capture these in order to compare the postoperative outcomes of the two imaging systems. Postoperative complications are classified and documented up to 90 days according to the internationally accepted Clavien-Dindo classification. In addition, the length of hospital stay is evaluated. The standard length of hospital stay is three nights or 4 days, defined from the day of surgery, which is also the day of admission, up to and including the day of discharge. Other outcomes of interest are confounding parameters that we will consider in the statistical analysis. These include age, sex, and BMI of the operated patients. Another possible parameter, if available, is the number of previous abdominal surgeries a patient has had. Previous abdominal surgeries, especially upper abdominal surgeries, may be a complicating factor and will be reported and considered accordingly. Furthermore, it is documented exactly which operation was performed by which of the three surgeons as well as their personal prevalence (2D 4K vs. 3D HD). This is to analyze a possible bias.

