**Fig. 2 Fig2:**
[figure not shown]
SPIRIT figure: Schedule of enrollment, interventions, and assessments. Asterisk symbol (*) indicates the following: if indicated in case of intraoperative complications. DOS, day of surgery; POD, postoperative day; LRYGB, laparoscopic Roux-en-Y gastric bypass; SURG-TLX, surgery task load index

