### Implementation {16c}

Patients are randomized 1 day before surgery using a computer-generated allocation list (generated using R version 4.1.3). The randomization list is linked to the study’s data management program (REDCap) by the project statistician. The operating surgeon recruits the patients and collects the data needed to conduct the study. The day before surgery, the surgeon enters the data into the electronic case report form (eCRF) in REDCap, which is designed for this study. Once the patient is enrolled in the study and the required data is entered into the system, the patient is automatically assigned to an intervention group using the linked randomization list. This ensures that surgeons have no influence on patient allocation. However, they are unblinded and are informed on the preoperative day which laparoscopic system will be used for the next surgery in the study. This is unavoidable, which is why our study is single-blind. Only the patients are blinded.

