## Data collection and management

### Plans for assessment and collection of outcomes {18a}

Data will be derived from electronic patient records and collected with an electronic case report form (eCRF) using REDCap electronic data capture tools hosted at the University of Basel. REDCap (Research Electronic Data Capture) is a secure, web-based software platform designed to support data collection for research studies [22, 23]. Laboratory testing is a standard part of the gastric bypass procedure and is performed in the central diagnostic laboratory of the University Hospital of Basel. The operative reports and other relevant information will be collected from the electronic patient records in the internal system of the University Hospital of Basel, and the information relevant to the study will be extracted and collected in the eCRF and in a folder created for the study. Only the study team has access to this specific study folder. The SURG-TLX is used to measure the surgeon’s workload immediately after surgery. The Surgery Task Load Index (SURG-TLX) is a validated multidimensional workload measure. It is a surgery-specific adaptation of the well-validated NASA-TLX and was proposed by Wilson et al. to assess the sources of workload perceived by surgeons in the operating room environment [24]. It has been used in robotic surgery in clinical settings and has been suggested to be useful in assessing human-machine interface issues and sources of stress caused by new technology in surgical practice. The questionnaire assesses operator workload along six dimensions:Mental demands: How mentally fatiguing was the procedure?Physical demands: How physically fatiguing was the procedure?Temporal demands: How hurried or rushed was the pace of the procedure?Task complexity: How complex was the procedure?Situational stress: How anxious did you feel while performing the procedure?Distractions: How distracting was the operating environment?

Postoperative complications are documented until 90 days postoperatively. Postoperative complications are classified into grades I–V according to the widely used and internationally accepted Clavien-Dindo classification [25].

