## Statistical methods

### Statistical methods for primary and secondary outcomes {20a}

Data will be analyzed using rpact (R package version 3.2.1) [21]. Descriptive statistics of primary and secondary endpoints will include minimum, maximum, standard deviation, mean, median, interquartile, 25th percentile, and 75th percentile for each study group.

The primary endpoint (mean OT) will be compared between study groups using an independent *t*-test. Since the distribution of OT is expected to be approximately symmetric with no outliers, the *t*-test is the primary choice. The tests will be one-tailed at a 2.5% significance level. Based on the O’Brian-Fleming alpha power function, the critical *p*-value is 0.0015 at the interim analysis and 0.0245 at the final analysis. Stop for futility is non-binding and set > 0. Acceptance of H1 will be concluded if alpha < critical values at the appropriate stages.

Study parameters other than OT are considered secondary. Secondary endpoints will be compared exploratorily using Mann-Whitney *U*-tests or Fisher’s exact tests, as appropriate. Tests will be two-tailed, alpha = 0.05.

Study groups will be exploratorily adjusted for age, sex, BMI, and possibly other parameters using regression analysis.

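### Hb decrease is measured only after certain intraoperative complications, yet the blanket rule for secondary parameters puts it under between-group tests; it should be reported descriptively

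*Protocol article*

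**What the plan says.** **Who has a value.** In Outcomes {12}, Secondary, "a postoperative Hb control is performed if indicated by intraoperative complications and the Hb decrease is determined". The legend of Fig. 2 attaches a condition of the same kind to an assessment marked with an asterisk: "if indicated in case of intraoperative complications". The figure itself is not shown.

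**What is done with it.** Statistical methods {20a} states: "Study parameters other than OT are considered secondary". It continues: "Secondary endpoints will be compared exploratorily using Mann-Whitney" U-tests or Fisher's exact tests, and "Tests will be two-tailed, alpha = 0.05". Hb decrease is not exempted.

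**What the condition depends on.** The Secondary section opens with "Secondary outcomes include intraoperative complications, operator workload, and postoperative complications", so the event that triggers the Hb control is itself an outcome. Under Implementation {16c}, "Patients are randomized 1 day before surgery using a computer-generated allocation list", and the surgeon knows the allocation; only patients are blinded.

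**Related measure.** The same Secondary section has blood loss recorded in millilitres, without a complication condition, and the abstract names blood loss as a secondary outcome.

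**The concern.** A between-group test estimates the effect of the imaging system only if the groups compared are those formed by randomisation. Here the Hb values would come from patients whose operation went wrong in a way that called for a blood test. If the imaging system affects how often or how severely that happens, the tested patients in the two arms are no longer alike. The adjustment for age, sex and BMI mentioned in {20a} does not undo this, because the selection acts after randomisation.

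What is at stake is the reading of one secondary result. A p-value from this subset, most likely a non-significant one, could be taken as a statement about bleeding when it reflects who was tested and how few they were.

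**Working it through.** The article gives no figure for Hb decrease, its spread or the intraoperative complication rate, so there is no stated figure to reproduce on this point. The primary sample size and critical values do reproduce (44.55 against the stated 44.6; one-sided p of 0.0015 and 0.0245), and this point does not touch them. All rates and Hb values below are assumptions.

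**1. How selection can shrink the difference.** Assume Hb drop is normal with SD 0.6 g/dL in both arms, the true mean difference is 0.30 g/dL in favour of 3D, and Hb is taken only when the drop exceeds a fixed cut. Set the 2D mean at 0. The mean above a cut z SDs above an arm's mean is: arm mean + SD × φ(z)/P(Z > z).

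- 2D: 15% tested gives z = 1.036 and φ(z) = 0.2332. Mean among tested = 0.6 × 0.2332/0.15 = 0.93.
- 3D: the same cut lies 0.30/0.6 = 0.5 SD further out, so z = 1.536, φ(z) = 0.1225 and the tested share is 0.0622. Mean among tested = 0.6 × 0.1225/0.0622 − 0.30 = 0.88.
- Difference among tested = 0.93 − 0.88 = 0.05 g/dL, against 0.30 in all patients.

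Varying the tested share in the 2D arm:

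| 2D tested | 3D tested | Difference among tested (g/dL) |
|---|---|---|
| 5% | 1.6% | 0.04 |
| 10% | 3.7% | 0.04 |
| 15% | 6.2% | 0.05 |
| 20% | 9.0% | 0.06 |
| 30% | 15.3% | 0.07 |

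This model selects on Hb drop itself, which is a strong form of selection. The protocol's trigger is mixed: organ injury, burns, circulatory problems and unexpected findings count as well as major bleeding. If the trigger were unrelated to Hb drop, the 0.30 would be preserved on average. The real distortion could therefore be smaller than shown.

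**2. How many patients would have a value.** With 48 patients allocated 1:1 there are 24 per arm. For an assumed rate p, equal in both arms, of complications that trigger an Hb control, the expected number with a value is 24p. The chance that at least one arm has none is 1 − [1 − (1 − p)^24]².

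| Assumed p | Expected per arm | P(at least one arm has none) |
|---|---|---|
| 5% | 1.2 | 50% |
| 10% | 2.4 | 15% |
| 20% | 4.8 | 1% |

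**3. What a test could show.** The smallest two-sided exact Mann-Whitney p with a and b untied values is 2/C(a+b, a).

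- 2 versus 3: 2/10 = 0.20
- 3 versus 3: 2/20 = 0.10
- 4 versus 4: 2/70 = 0.029

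With 3 or fewer values in each arm, p < 0.05 cannot be reached whatever the data.

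**The case against.** The strongest reply is that the plan does not really commit to this test. Hb decrease appears neither in the opening list of secondary outcomes nor in the abstract; it enters only through the blanket sentence in {20a}. Read literally, that sentence would also sweep in age, sex and BMI, which the Secondary section treats as confounders. It is loose wording. {20a} also says the tests are used as appropriate, and the Secondary section says intraoperative complications are assessed in a descriptive way, with Hb following as an add-on.

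Part of this stands. Hb decrease is not a named outcome, and that lowers the weight of the point. The other two phrases do not settle it. The first most naturally chooses between Mann-Whitney and Fisher. The second describes how complications are ascertained, from the surgeon's operative report. Neither says that Hb decrease is left untested.

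It is also fair that bleeding already has a measure recorded without this condition, blood loss in mL, and that every secondary comparison is labelled exploratory. Both stand and limit the consequence.

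A reader might go further and infer that the Hb comparison would reverse the true direction. An example can be built: with assumed mean drops of 1.0, 1.5 and 3.0 g/dL for no, minor and major complications, and rates of 4% minor and 6% major in one arm against 16% and 8% in the other, the means are 1.14 versus 1.24 in all patients but 2.40 versus 2.00 among those tested. That mix is hand-picked and nothing in the article supports it. The calculation in step 1 shows shrinkage, not reversal.

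**Conclusion.** The point holds as a modest one. As written, the article measures Hb decrease in a subset selected after randomisation and, through its blanket rule, puts it under between-group tests. Such a comparison is not one of the randomised groups and can distort the difference. Under the stated assumptions 0.30 g/dL becomes about 0.05; across tested shares of 5% to 30% in the 2D arm it becomes 0.04 to 0.07. These figures rest on an assumed SD, effect and testing rule and show what can happen, not what will. At assumed rates of 5% to 20%, a test would rest on about 1 to 5 values per arm.

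The primary outcome, the sample size and the interim and final critical values are not affected. Nor does the point show that the trial's assessment of bleeding as a whole is unsound, since blood loss in mL is recorded without the condition. A reader might also infer from "Laboratory testing is a standard part of the gastric bypass procedure and is performed in the central diagnostic laboratory" that Hb values already exist for everyone. That sentence does not say a postoperative Hb is taken in every patient, and the conditional wording in the Secondary section points the other way.

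**What to change.** In Statistical methods {20a}, add a sentence saying that Hb decrease is reported descriptively, with the number of patients measured in each arm, and is not tested between groups. Add that blood loss in mL is the between-group comparison for bleeding. Align the Secondary section of Outcomes {12} with this.

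The cost is a line or two of wording and the loss of one exploratory p-value that could not be interpreted. No change to sample size or data collection is needed, and no change to clinical testing is proposed.
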